
### Measures, procedures, and analyses by study aim

All of the below measures will be collected for 3 years: during the 2-year GTO period of support and 1 year after that support ends to assess sustainability (see aim 4 below).

#### Aim 1: compare MISSION-Vet fidelity between GTO and IU groups

*Data source*. Veterans served by case managers in the GTO and IU groups.

*Measures and data collection.* The MISSION-Vet Fidelity Measure tracks all the core elements of the MISSION-Vet treatment model, including CTI, DRT, peer support, vocational supports, and trauma-informed care for each individual Veteran. The fidelity index consists of 78 items assessing the presence or absence of certain activities within MISSION-Vet. Taking the responses from all non-missing items, we will compute a fidelity score for each Veteran. The data will be extracted from the VA Computerized Patient Record System (CPRS) on all HUD-VASH Veterans served by case managers in the IU or GTO conditions, at each of the three HUD-VASH sites.

*Hypothesis.* We expect that Veterans served by case managers who were in the GTO group will receive MISSION-Vet with greater fidelity compared to those who are in the IU group.

*Data analysis.* We will fit cross-sectional linear random effects (to account for clustering) models for the fidelity score, measured at 12 months post-baseline.

#### Aim 2: compare the effect on the proportion of time the Veteran is housed between GTO and IU groups

*Data sources*. Veterans served by case managers in the GTO and IU groups.

*Measures and data collection*. For each Veteran entering HUD-VASH, a case manager must complete a HUD-VASH Referral Worksheet that contains the program’s first assessment of days of homelessness and housing. Then, case managers provide data every 3 months on the number of days housed in the last 90 days using the Housing Progress Report form. Case managers are also required to report when a Veteran loses their housing voucher each month. These reports are stored in national database called HOMES (Homeless Operations, Management and Evaluation System).

*Hypothesis*. We expect that Veterans assigned to case managers in the GTO group, who receive MISSION-Vet, will have more days housed in the prior 3 months compared to Veterans who receive MISSION-Vet from case managers in the receiving IU group.

*Data analysis*. Again, we will fit repeated measures linear random effects models in this analysis. As a secondary analysis, we will perform a *z* test for the comparison of the proportion of Veterans at the end the study who have retained their housing (versus lost their voucher) between GTO versus IU.

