## Methods

### Overview

This project is a Hybrid Type III, cluster randomized controlled trial [19] that compares MISSION-Vet Implementation as Usual (IU—standard training and access to the MISSION-Vet treatment manuals) to MISSION-Vet implementation augmented by GTO. This study is being carried out in HUD-VASH teams at three large VA Medical Centers over a 2-year period. Within each site, existing sub-teams (case managers and Veterans they serve) are the clusters that will be randomly assigned, which is particularly appropriate when desiring to lessen the risk of experimental contamination [20] of the implementation strategy. Blinding in the traditional sense—e.g., data collectors blinded to subjects’ treatment assignment—will not be possible; however, all data will be coming from secondary sources. As a Hybrid Type III trial, it will emphasize the test of an implementation strategy (GTO), while using VA’s existing HUD-VASH data monitoring system to also assess the effectiveness of the treatment (MISSION-Vet) [21] called *HOMES* (Homeless Operations, Management and Evaluation System). This design is appropriate when the implementation strategy has strong preliminary evidence, the EBP in question has solid evidence but could yield weaker outcomes in new or less controlled environments than was present in efficacy trials, and the EBP has “implementation momentum” [21]. These conditions are present for implementing MISSION-Vet in HUD-VASH, as will be shown below. The trial assesses three sets of variables: a) MISSION-Vet implementation (adoption, dose, reach, fidelity), b) outcomes among HUD-VASH Veterans (mental health and substance use, community functioning, housing), and c) MISSION-Vet implementation barriers and facilitators organized by the CFIR.

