#### Recruitment

The subjects in this study are the HUD-VASH case managers although data about the Veterans on their caseload will also be collected. All case managers were invited to participate and consented before randomization by the study staff. The two sub-teams from each site that were assigned to GTO or IU have approximately equal numbers of case managers and vouchers, although the exact numbers shift frequently due to staff turnover and Veteran dropout, graduation, and the issuing of new vouchers. Regardless, consistent with cluster random assignment, each case manager is linked to a certain sub-team (and thus study condition), and each Veteran is in turn linked to a specific case manager. If sites decide to add new staff to a sub-team, that case manager would then automatically be assigned to the condition of that sub-team.

All HUD-VASH case managers in both groups will be invited to the webinar training on MISSION-Vet. After MISSION-Vet begins, case managers will be responsible for engaging their Veterans into MISSION-Vet services. Any Veteran participating in HUD-VASH at each of these three sites is eligible to receive MISSION-Vet services. Through training and TA, case managers and peer specialists will be guided to follow the recommended inclusion and exclusion criteria of MISSION-Vet: (1) has a current substance abuse or dependence disorder and a co-occurring mental illness and (2) is willing to participate in MISSION-Vet services. However, the decision with whom to deliver MISSION-Vet will ultimately be made by the case managers. MISSION-Vet takes about 1 year to fully deliver; therefore, Veterans will be invited to take part in MISSION-Vet in the first year of the 2-year intervention period. The study received a waiver of consent to use client-level data already being collected as part of the homeless data program management system of HUD-VASH.

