*Data analysis*. The scores for R, E, A, and I will be calculated among the Veterans in both the GTO and IU groups during the 2-year period of GTO support. For *Reach*, we will perform a *z* test for the comparison of the proportion of Veterans at the end of the GTO period with adequate fidelity between GTO versus IU. The *Effectiveness* analysis will involve *t* tests comparing mean scores at the end of the GTO period for the proportion of time housed and homeless (on the logit scale), components of the ASI, and the GAF. For *Adoption*, we will compare the proportion of case managers through a *z* test who have “adopted” MISSION-Vet according to the specified measure. We will also perform a logistic regression of whether a case manager adopted MISSION-Vet as a function of study arm, one of the moderating variables, and their interaction, testing specifically for the interaction term. The analysis of *Implementation* will compare through a *z* test the proportion of Veterans who participated in MISSION-Vet who had a fidelity score of at least 75 % between the GTO versus IU groups.

*Maintenance*—The analyses described above for R, E, A, and I will be similarly applied to the data collected and summarized a year after the end of the GTO support period.

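### The secondary test of voucher retention in Aim 2 is a plain z test of proportions that ignores unequal time at risk and clustering, at a time point that is not defined

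*Protocol article*

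**What the plan says.** In the Protocol article, Aim 2, the main analysis of days housed is a repeated measures random effects model. Voucher loss gets one further test, labelled secondary. It is a z test, and its target is given as "comparison of the proportion of Veterans at the end the study who have retained their housing (versus lost their voucher"). The same section describes richer data than that test uses: "Case managers are also required to report when a Veteran loses their housing voucher each month".

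The Recruitment section describes an open caseload. The sub-teams start with roughly equal numbers, "although the exact numbers shift frequently due to staff turnover and Veteran dropout, graduation, and the issuing of new vouchers". Site composition also expects the number of vouchers to change over time, and gives two sub-teams per site at three sites.

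The document does not say when the study ends for this test. Under Measures, procedures, and analyses: "All of the below measures will be collected for 3 years: during the 2-year GTO period of support and 1 year after that support ends". Under Overview: "This study is being carried out in HUD-VASH teams at three large VA Medical Centers over a 2-year period". Aim 4 has its own wording for the end of support, "comparing mean scores at the end of the GTO period for the proportion of time housed and homeless", and repeats its analyses one year later under Maintenance. Voucher retention is not among the measures named there.

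**The concern.** This is the only analysis named for voucher loss, and it has three weaknesses.

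- **Time at risk.** Someone issued a voucher late has had less time to lose it. If the arms differ in when Veterans entered, the proportions who kept a voucher will differ with no effect of GTO. Three sub-teams per arm are too few for randomisation to make entry patterns alike.
- **Clustering.** Veterans are grouped under case managers, who are grouped in sub-teams. The main Aim 2 model has random effects and the power section uses a design effect. A two-proportion z test has neither.
- **Time point.** If the status is read at month 36, losses during support and in the year after it are pooled, so the result answers neither the question about support nor the one about sustainability.

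A difference in voucher retention could then be declared that reflects caseload turnover or case-manager differences rather than GTO.

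**Working it through.** **1. The plan's own figures (Power analysis).** Veterans: 2110 × 0.80 × 0.95 = 1603.6, stated as 1604. Per case manager: m = 1604/66 = 24.3. Design effect: 1 + (24.3 − 1) × 0.15 = 4.495. Effective sample: 1604/4.495 = 356.8, stated as 356 and used for Aims 2 and 3. These reproduce. No voucher-loss rate, effect or power is given, so the rates below are assumptions.

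**2. Clustering.** If the true variance is Deff times what the z test assumes, its type I error at a two-sided 5 % level is 2 × [1 − Φ(1.96/√Deff)]. With Deff = 4.495, √Deff = 2.120 and 1.96/2.120 = 0.924, which gives 0.355, or about 36 %. The ICC of 0.15 is the protocol's conservative choice and may be too high for voucher loss. With assumed lower values:

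| ICC | Deff = 1 + 23.3 × ICC | Type I error |
|---|---|---|
| 0.01 (assumed) | 1.233 | 7.8 % |
| 0.05 (assumed) | 2.165 | 18.3 % |
| 0.15 (protocol) | 4.495 | 35.5 % |

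**3. Time at risk, no true effect.** Assume 802 Veterans per arm (1604/2), 1 % monthly loss, follow-up to month 36 and independent Veterans. A Veteran present from the start has lost the voucher by month 36 with probability 1 − 0.99^36 = 0.304. The average for a late entrant is 0.256 if entry is uniform over months 1–12, and 0.157 if uniform over months 1–36. With a share w of late entrants, an arm's expected loss is (1 − w) × 0.304 + w × late-entrant loss. The standard error of a difference is √(2p(1 − p)/802), about 0.022.

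| Late entry over | Late share by arm | Expected loss | Spurious difference | z-test rejection |
|---|---|---|---|---|
| months 1–12 | 40 % v 30 % | 0.285 v 0.289 | 0.005 | 5.5 % |
| months 1–12 | 40 % v 20 % | 0.285 v 0.294 | 0.009 | 7.0 % |
| months 1–36 | 40 % v 30 % | 0.245 v 0.260 | 0.015 | 10.4 % |
| months 1–36 | 40 % v 20 % | 0.245 v 0.274 | 0.029 | 26.9 % |

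Simulations of the same set-up gave 4–7 % for the first pair and 10–27 % for the second. A log-rank test on monthly times from entry gave 3–6 % throughout.

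A simpler view compares mean follow-up of 2.0 and 2.5 years with no effect. At 10 % annual loss the spurious difference is 0.9^2 − 0.9^2.5 = 0.810 − 0.768 = 0.042. At 5 % and 20 % it is 0.023 and 0.068.

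**4. Reading at month 36.** Assume 10 % annual loss under IU, a hazard ratio of 0.6 during support, and the protocol's effective 178 per arm (356/2).

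- Month 24: 0.81^0.6 − 0.81 = 0.881 − 0.810 = 0.071; z-test power 0.46 (log-rank 0.47).
- Month 36, effect stops with support: 0.881 × 0.9 − 0.729 = 0.793 − 0.729 = 0.064; power 0.29.
- Month 36, effect persists: 0.729^0.6 − 0.729 = 0.827 − 0.729 = 0.098; power 0.61.

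The direction depends on persistence. With equal follow-up, the time-to-loss form adds almost no power at the same horizon.

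**The case against.** The strongest reply is that the test is secondary and that housing during support is examined elsewhere: days housed is modelled every three months, and Aim 4 compares housing time at the end of GTO support. That stands and limits the weight of the point, although neither analysis tests voucher loss.

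Second, Veterans are invited into MISSION-Vet in the first year and the sub-teams start with similar numbers. If the test is confined to those Veterans and late entry ends in year 1, the time-at-risk error is small (4–7 %). That also stands. But the stated data source is the Veterans served by the case managers, and new vouchers are not limited to year 1.

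Third, an article may leave such detail to an analysis plan, and the Design challenges section says that case-manager clustering is accounted for in the analyses. Here, however, the method is named, and a z test of two proportions does not account for clustering.

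A reader might infer more: that the year after support necessarily dilutes the effect, or that unused monthly data cost much power. The documents support neither. The end of the study reads most naturally as year 3, since Aim 4 words the end of support differently, but it is undefined and the Overview speaks of two years. The protocol also hopes that GTO practices become routine and expects better maintenance with GTO. If the effect persists, month 36 has more power than month 24.

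**Conclusion.** The concern holds for validity, not as a claim of lost power. The named z test is unsuited to an open, clustered caseload. Ignoring clustering is the larger fault: about 36 % type I error at the protocol's own design effect, and still about 18 % at an assumed ICC of 0.05. Unequal time at risk adds from almost nothing to a rejection rate of about 27 %, depending on how late and how unequal entry is. That range rests on assumed loss rates and entry patterns, and arises only if entry differs between arms. Pooling losses during and after support is a matter of clarity; it weakens the comparison only if month 36 is meant and the effect fades. Because the analysis is secondary, the point is minor to moderate.

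**What to change.** In Aim 2, Data analysis, replace the z test with a discrete-time or Cox model of monthly voucher loss. Count time from the later of site start and voucher issue, and carry over the clustering terms of the main models. Treat graduation and dropout as exits separate from voucher loss, either censored or competing, and say which. State which month the end of the study means for this analysis. Report retention from the fitted curves at the end of GTO support (month 24) and one year later (month 36), in line with the split Aim 4 already makes. Giving both readings avoids betting on whether the effect persists; making month 24 the sole main reading would be a trade-off.

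The cost is wording and code, since the monthly loss reports are already in HOMES. A hazard ratio is slightly harder to read than a proportion, which the fitted retention figures offset. Standard errors will be wider once clustering is allowed for.

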#### Aim 3: compare mental health, substance use, and functional outcomes among Veterans served by HUD-VASH case managers in GTO and IU groups

*Data sources*. Veterans served by case managers in the GTO and IU groups.

*Measures and data collection*. In addition to housing, the HUD-VASH staff complete data collection forms for HOMES on four outcomes each month. HOMES requires case managers to make separate ratings on mental health, substance abuse, and associated problems for each Veteran using components of the Addiction Severity Index [46] as well as the Global Assessment of Functioning (GAF) [47].

*Hypothesis*. We expect that Veterans served by HUD-VASH case managers supported by GTO, who received MISSION-Vet, will have improved mental health, substance use, and functional outcomes compared to Veterans served by HUD-VASH case managers in the IU group.

*Data analysis*. We will again fit our repeated measures linear random effects models to the response variables mentioned above.

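### The Aim 2 and Aim 3 hypotheses condition on receipt of MISSION-Vet, a post-randomisation choice, while the rest of the plan points to all Veterans served

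*Protocol article*

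**What the plan says.** Four parts of the protocol article bear on who is compared in Aims 2 and 3.

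- **Aim 2, Hypothesis.** The GTO side is "Veterans assigned to case managers in the GTO group, who receive MISSION-Vet, will have more days housed in the prior 3 months". The IU side is also limited to recipients: "compared to Veterans who receive MISSION-Vet from case managers in the receiving IU group".
- **Aim 3, Hypothesis.** The GTO side again carries a receipt clause: "Veterans served by HUD-VASH case managers supported by GTO, who received MISSION-Vet, will have improved mental health, substance use, and functional outcomes". The IU side does not: "compared to Veterans served by HUD-VASH case managers in the IU group".
- **Aims 2 and 3, headings, Data sources and Data analysis.** The Data sources line is the same in both aims: "Veterans served by case managers in the GTO and IU groups". The headings name the two groups. The Data analysis lines name the model and add no receipt condition.
- **Power analysis.** The 1604 Veterans come from 2110 vouchers after reductions for absence of co-occurring substance use disorder and for case manager refusal. Aims 2 and 3 use the same effective 356, described as Veterans with a full year of quarterly data.

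The Recruitment section says how receipt comes about. "After MISSION-Vet begins, case managers will be responsible for engaging their Veterans into MISSION-Vet services". The recommended criteria include that the Veteran "is willing to participate in MISSION-Vet services", and "the decision with whom to deliver MISSION-Vet will ultimately be made by the case managers".

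**The concern.** Sub-teams are randomised; receipt of MISSION-Vet is not. Receipt is decided later, by case managers who know their arm and by Veterans who agree or decline. GTO is meant to act on that decision, and the Aim 4 hypothesis expects better Reach and Adoption under GTO. Selecting Veterans on receipt therefore selects on something that the randomised strategy may have altered, and a random effect for case manager does not undo that.

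The two hypotheses are exposed in different ways. In Aim 2, recipients in the two arms may be different kinds of Veteran if GTO widens or narrows who is engaged. In Aim 3 as worded, a selected group faces an unselected one, so the groups can differ even if uptake is identical in both arms.

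At stake is whether a difference in housing, mental health, substance use or functioning could be attributed to GTO. A reader of the results would also be unable to tell which population had been planned.

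**Working it through.** **1. The plan's own figures.**

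- N = 2110 × 0.80 × 0.95 = 1603.6 (stated 1604).
- Deff = 1 + (24.3 − 1) × 0.15 = 4.495, and 1604 / 4.495 = 356.8 (stated 356).
- Detectable time-by-intervention effect: noncentral F with λ = f² × N × 5 / (1 − ρ), df 4 and 4(N − 2), N = 356, 80 % power, α = 0.05. This gives f = 0.0820 at ρ = 0 (stated 0.082).

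All of these reproduce. The chain contains two reductions, 20 % and 5 %, and neither is for non-receipt. The sample size therefore describes Veterans with co-occurring disorders whether or not they received MISSION-Vet.

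**2. The populations side by side.**

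| Place | GTO side | IU side |
|---|---|---|
| Aim 2 Hypothesis | recipients | recipients |
| Aim 3 Hypothesis | recipients | all served |
| Aims 2 and 3 headings, Data sources | all served | all served |
| Power analysis, Aims 2 and 3 | 12 months of data, no receipt condition | same |

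These cannot all describe one analysis set, and no sentence says which governs.

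**3. What a recipients-only set would do to the sample size.** The article gives no uptake figure, so uptake u is an assumption here, taken as equal in both arms. With 66 case managers and ICC 0.15: n = 1604u, m = n / 66, Deff = 1 + (m − 1) × 0.15, effective N = n / Deff, and f as in step 1 with ρ = 0.

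| u (assumed) | n | Deff | effective N | detectable f |
|---|---|---|---|---|
| 75 % | 1203 | 3.584 | 336 | 0.0845 |
| 50 % | 802 | 2.673 | 300 | 0.0894 |
| 25 % | 401 | 1.761 | 228 | 0.1027 |
| 10 % | 160 | 1.215 | 132 | 0.1351 |

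The stated 356 and 0.082 go with the all-Veterans reading and not with recipients only. The loss of precision is modest until uptake is low. The main issue is bias.

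**4. The form of the bias under no true effect.** Let c_R and c_N be the mean change over the year in Veterans who would and would not be chosen, with the same selection in both arms. The Aim 3 wording then estimates

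c_R − [u·c_R + (1 − u)·c_N] = (1 − u)(c_R − c_N).

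- If recipients differ from non-recipients only by a constant level, c_R = c_N and the time-by-intervention contrast is zero.
- If their trajectories differ, the contrast is not zero even with equal uptake.

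For the Aim 2 wording, the null contrast is mean change in GTO recipients minus mean change in IU recipients. It is zero when the two recipient groups have the same underlying trajectory, which randomisation does not guarantee. The article gives neither u nor c_R − c_N, so no numerical bias follows from it.

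**The case against.** The strongest reply is that no recipients-only analysis is actually fixed. The receipt clause stands in two hypothesis sentences, while the headings, Data sources, Data analysis lines and sample size all run by assigned group. In Aim 3 the clause is set off by commas and may be a loose description of the GTO group. An article may also leave the exact analysis set to a fuller document.

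Much of this stands. A reader might infer that the trial has committed itself to comparing GTO recipients with all IU Veterans. The text does not establish that; it establishes a contradiction. What does not stand is that the point can be left as silence for another document to fill. The article states the populations, and they disagree. The comma reading does not help Aim 2, whose IU comparator is plainly restricted to recipients.

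A reader might also set an assumed prognostic gap between recipients and others against the detectable effect of 0.298 and call the bias a large share of it. That comparison is not supported. The 0.298 is the Aim 1 two-sample effect for fidelity, whereas Aims 2 and 3 are sized on a time-by-intervention effect of 0.082 on a different scale. The Power analysis also relies on each Veteran being compared with himself or herself over time, which removes a stable difference in level.

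Finally, this is a Hybrid Type III trial that puts implementation first and effectiveness second, and Aim 1 is not touched. That lowers the severity.

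**Conclusion.** The point holds as an unresolved contradiction about the population for Aims 2 and 3. Two stated hypotheses, if tested as worded, would be non-randomised comparisons, and in Aim 3 the two sides would be defined differently. The other statements in the article point to all Veterans served.

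The conclusion rests on the article's own account that receipt follows randomisation, depends on the case manager and the Veteran, and is a target of GTO. The direction and size of any bias are unknown. It would depend on uptake and on how far the trajectories of recipients and non-recipients differ, and neither is given. The sample sizes in the uptake table rest on assumed uptake and serve only to show which reading the stated 356 matches.

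This should be fixed, but it does not threaten the main aim of the trial.

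**What to change.** Reconcile the Aim 2 and Aim 3 hypotheses with the Data sources lines and the Power analysis, as follows.

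- State the primary comparison for both aims as all Veterans in GTO against IU sub-teams, by assigned sub-team and regardless of whether MISSION-Vet was delivered.
- Delete the receipt clause from both hypotheses, on both sides in Aim 2.
- If the set is limited to co-occurring disorders, to match the 1604, define this from diagnoses recorded before randomisation, or at HUD-VASH entry for Veterans who join later, identically in both arms. An undated chart diagnosis could itself be affected by arm.
- Say how the subsample with 12 months of data in the Power analysis relates to this population.
- Report recipient-only results with one definition in both arms, labelled descriptive and non-randomised.

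The cost is mostly wording. HOMES is described as collecting housing and clinical ratings on HUD-VASH Veterans without reference to receipt. A diagnosis extract may be needed, since the article describes extraction from the medical record only for MISSION-Vet service and fidelity data. The real downside is that the estimated effect is diluted by Veterans who never receive MISSION-Vet. That is the effect of assigning a sub-team to GTO, and it is what the randomisation can support.
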